|------------------------------|---------------------------------------------------------------------------------------------------------------------------------------------------------------------------------------------------------------------------------------------------------------------------------------------------------------------------------------------------------------------------------------------------------------------------------------------------------------------------------------------------------------------------------------------------------------------------------------------------------------------------------------------------------------------------------------------------------------------------------------------------------------------------------------|
|                              | 
 
● Disseminated intravascular coagulation or active bleeding;
 
● Allergy to heparin or insulin;
 
● Usage of any triglyceride-lowering treatments between symptoms onset and randomization, or blood purification treatment for acute renal failure;
 
● Cardiopulmonary resuscitation for cardiac arrest;
 
● Patients with irreversible organ failure or other critical manifestations who are expected to die within 24 hours;
 
● Advanced malignant tumors, immunodeficiency disorders, and a pre-existing chronic renal failure requiring regular hemodialysis;
 
● Conscious and behavioral abilities are partially or totally limited and unable to make decisions independently.
 
 |
| Treatments            | 
LMWH + insulin group
 
a 4000 IU of LMWH sodium injection (enoxaparin) will be injected subcutaneously once every 12 hours for three days.
 
Insulin adjusted on the glucose levels.
 
Insulin alone group
 
Insulin adjusted on the glucose levels.
                                                                                                                                                                                                                                                                                                                                                                                                                                                                                         |

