### **3.4 Exclusion criteria**

- Biliary pancreatitis defined as the presence of dilated choledocholith, or meeting two of the following three laboratory abnormalities: (1) serum bilirubin concentration >1.9 mg/dL; (2) alanine aminotransferase (ALT) activity >100 U/L with ALT activity higher than the aspartate aminotransferase (AST) activity; and (3) alkaline phosphatase activity >195 U/L with  $\gamma$ -glutamyltransferase (GGT) activity >45 U/L;
- Alcoholic pancreatitis defined as a history of over 5 years of heavy alcohol consumption (>50 g per day);
- Pregnant or lactating females;
- Disseminated intravascular coagulation or active bleeding;
- Allergy to heparin or insulin;
- Usage of any TG-lowering treatments (including TG-lowering drugs, plasma exchange, or haemofiltration) between symptoms onset and randomisation, or blood purification treatment for acute renal failure;
- Cardiopulmonary resuscitation for cardiac arrest;
- Patients with irreversible organ failure or other critical manifestations who are expected to die within 24 hours, including patients with severe ARDS requiring extracorporeal life support ( $\text{FiO}_2/\text{PO}_2 < 60$  if  $\text{PEEP} > 10$  cm  $\text{H}_2\text{O}$  and  $\text{FiO}_2 = 100\%$ ), severe systemic circulatory failure (a systolic blood pressure <90 mmHg and serum pH values <7.0 given full-fluid resuscitation and norepinephrine usage at a dose of 25  $\mu\text{g}/\text{min}$ ), or severe coma without sedation drugs with a Glasgow score equal to three points;
- Advanced malignant tumours, immunodeficiency disorders, and a pre-existing chronic renal failure requiring regular haemodialysis;
- Conscious and behavioural abilities are partially or totally limited and unable to make decisions independently.

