### **4.3 Intervention Group (LMWH + insulin group)**

In the LMWH + insulin group, a 4000 IU of LMWH sodium injection (enoxaparin) will be injected subcutaneously once every 12 hours for three days. Continuous usage of LMWH at prophylactic dosages will be considered for patients assessed to be at high-highest risk of venous thromboembolism and low bleeding risk, which was on chief physician's discretion.

For those with a glucose level > 11.1 mmol/L, patients will receive micropumps of insulin at 2 to 6 U/h, monitor blood glucose closely, to maintain the serum glucose levels between 7.8 and 10 mmol/L. When the glucose levels fall below 7.8 mmol/L, 6 U of insulin will be added to 500 mL of 5% glucose for intravenous infusion until the TG levels decrease to less than 5.65 mmol/L (500 mg/dL) or for a maximum duration of 5 days after randomization, whichever occurs first. For those with a glucose level ≤11.1 mmol/L, patients will receive 6 U of insulin with 500 mL of 5% glucose for intravenous, twice a day for 5 days, if hypoglycemia occurs, 5% dextrose change to 10% dextrose.

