### **4.5 Drug Withdrawal Standard**

When TG levels reach less than 500 mg/dL or at 5 days after enrollment, insulin will

be stopped and oral lipid-lowering drugs will be administered in the above two groups. If the blood glucose level is still greater than 11.1 mmol/L, insulin will be maintained to control the blood sugar. While LMWH administration was limited to 3 days (irrespective of triglyceride levels) in the LMWH + Insulin Group. However, LMWH (4000 IU every 12 hours for 7-10 days) was administered as venous thromboembolism (VTE) prophylaxis in high-risk patients (Padua score  $\geq 4$ ), and with low bleeding risk in both groups.

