## 5 OUTCOMES

### 5.1 Primary endpoint

The primary endpoint is a composite of new-onset organ failure and mortality within one month after randomization, excluding events occurring within 24 hours before randomization. Organ failure includes respiratory failure, renal failure, and circulatory failure, which is defined as a score of 2 or more using the modified Marshall scoring system^28.

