## **10 Discussion**

This study was the first randomized trial comparing LMWH plus insulin versus insulin alone in patients with HTG-AP admitted within 48 hours. The initial version of the study protocol was a multicenter, prospective, single-blind, randomized controlled trial, which was published in *Pancreas*. However, before the study was initiated, the protocol was revised after all the research centers discussed it: firstly, the ethical committees at some centers reviewed that LMWH was also needed for patients entering the insulin group who were at very high risk of thrombosis. In addition, patients at 48 hours of onset endured pain, and the additional subcutaneous injection of placebo (saline) in the control group added to patient suffering, so changing from single-blind to open-label was recommended due to poor feasibility; secondly, statisticians recommended revising the sample size from 476 to 540 cases based on the calculations of a superiority trial; thirdly, experts recognized that acute renal failure increases the risk of hemorrhage with LMWH, and that these patients need to undergo blood purification, which affects TG levels, so they were excluded. Finally, we retracted the original protocol after discussion, and the revised protocol was approved by the Ethics Committees and updated in the Clinical Trial Registry(<https://www.chictr.org.cn/showproj.html?proj=28529>).

The reason for placing an upper limit on TG levels will be based on the ethics committee's advise; prior to the initiation of this study, several research centers routinely placed patients with TG >3550 mg/dL on plasma exchange in clinical practice, as it has been reported that hemodialysis of patients with extremely high levels of serum TG shortens the length of hospital stay.

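### Section 10 says patients with acute renal failure were excluded because of LMWH bleeding risk, but the exclusion criterion removes only those on blood purification for it

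*Protocol*

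**What the plan says.** Section 10 (Discussion) lists the revisions made before the study started. The third concerns kidney function. It records that "experts recognized that acute renal failure increases the risk of hemorrhage with LMWH", and continues that "these patients need to undergo blood purification, which affects TG levels, so they were excluded". The patients referred to are those with acute renal failure.

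The operative rule is in section 3.4. One item excludes earlier triglyceride-lowering treatment "between symptoms onset and randomisation, or blood purification treatment for acute renal failure". The exclusion list in the synopsis has the same clause: "between symptoms onset and randomization, or blood purification treatment for acute renal failure". Both name a treatment given for acute renal failure, not the condition.

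In the LMWH + insulin group, section 4.3 gives enoxaparin 4000 IU that "will be injected subcutaneously once every 12 hours for three days". LMWH beyond that course is considered for patients "at high-highest risk of venous thromboembolism and low bleeding risk", at the chief physician's discretion. Section 4.5 allows prophylactic LMWH in patients with a Padua score of 4 or more "and with low bleeding risk in both groups".

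**The concern.** The rationale and the rule describe different groups. The bleeding reason in section 10 attaches to acute renal failure itself, whether or not purification has begun. The criterion applies only when purification is being used.

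Sites enrol from section 3.4. If they follow it literally, a patient with acute renal failure who is not on purification can be randomised to LMWH, an exposure the protocol itself calls a haemorrhage hazard. The clause also leaves open whether purification that is indicated or planned counts, so up to 10 centres could apply it differently. What is at stake is the safety of these patients and consistent eligibility across centres.

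**Working it through.** The claim rests on comparing texts, and the plan states no figure for it. The arithmetic below only sets the scale and the cost of a change.

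**1. Does another criterion in section 3.4 close the gap?**

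| Criterion | Covers acute renal failure without purification? |
|---|---|
| Blood purification for acute renal failure | No: requires the treatment |
| Chronic renal failure | No: must be pre-existing and on regular haemodialysis |
| Irreversible organ failure or other critical state | No: requires expected death within 24 hours; the examples given are respiratory, circulatory and neurological |
| Disseminated intravascular coagulation or active bleeding | No: covers present coagulopathy or bleeding, not raised risk |

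Section 3.4 sets no creatinine, clearance or Marshall renal limit.

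**2. Can such a patient present?** Section 3.3 requires randomisation within 48 hours of onset, so renal failure may be present before purification has started. Section 5.1 counts renal failure as an organ failure and defines the endpoint "excluding events occurring within 24 hours before randomization". The protocol therefore foresees organ failure at entry.

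**3. Does a later safeguard apply to the three-day course?** Low bleeding risk is required in 4.3 for continued LMWH and in 4.5 for prophylaxis. The randomised course has no renal or bleeding-risk condition, although the prophylactic dose in 4.5 is the same 4000 IU every 12 hours.

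**4. Exposure per affected patient on LMWH** (section 4.3)

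- Doses: 3 days × 2 per day = 6
- Total: 6 × 4000 IU = 24,000 IU

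**5. Scale** (540 randomised 1:1, section 8.1)

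- Each 1% of patients: 540 × 0.01 = 5.4
- On LMWH: 5.4 / 2 = 2.7

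The true percentage is not in the documents.

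**6. Recruitment cost of excluding them** (36 months' recruitment, synopsis)

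- Planned rate: 540 / 36 = 15 per month
- Replacements per 1% excluded: 540 / 0.99 − 540 = 5.45
- Added time: 5.45 / 15 = 0.36 months

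**7. Effect on power if the control event rate moves.** Section 8.1 assumes 17.86% on insulin alone and 8.3% on the combination, with 490 evaluable patients, or 245 per group. The relative risk is 8.3 / 17.86 = 0.465. Let pC be the control rate, pT = 0.465 × pC, p̄ their mean and n = 245. Then

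power = Φ{ [(pC − pT) − 1.96 √(2p̄(1 − p̄)/n)] / √([pC(1 − pC) + pT(1 − pT)]/n) }

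| Control rate | Power |
|---|---|
| 17.86% | 88.3% |
| 16% | 84.0% |
| 15% | 81.3% |
| 14.56% | 80.0% |
| 14% | 78.2% |

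The 88.3% in the first row exceeds the 80% stated in section 8.1. That difference is a separate matter and does not bear on this point.

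**The case against.** The strongest counter-reading is that section 10 describes a single group, patients with acute renal failure who need purification, and that section 3.4 names that group in shorter form. Section 10 is also a narrative of how the protocol changed, while 3.4 and the synopsis agree with each other and are what sites use. Section 5.1 fits 3.4 as written: it sets aside organ failure in the 24 hours before randomisation with no renal exception, so baseline renal failure may have been meant to stay eligible. On that view only the Discussion is loosely worded, and a new renal threshold would be the reviewer's preference.

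Part of this stands. The intention is uncertain, the documents do not fix a cut-off, and correcting section 10 is a legitimate way out. But the one-group reading does not remove the gap. The bleeding reason is not limited to patients on purification. Even if indicated purification counted, acute renal failure not needing it would remain eligible. And section 10 describes the change that was adopted, not superseded text.

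Other protections exist: the exclusion of disseminated intravascular coagulation and active bleeding, bleeding as a safety endpoint, serious adverse event reporting, six-monthly IDMC review, and open-label treatment, so clinicians know who receives LMWH. None of them screens for acute renal failure before the first dose.

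**Conclusion.** The concern holds. As written, section 3.4 and the synopsis do not exclude acute renal failure without blood purification, although section 10 says these patients were excluded and gives bleeding risk as one of its reasons. Each affected patient allocated to LMWH would receive up to 24,000 IU with no renal or bleeding-risk condition beyond the exclusion of disseminated intravascular coagulation and active bleeding.

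The number affected cannot be derived from the documents and is not estimated; the per-1% figures are scale only. An investigator might decline to enrol such a patient, but the protocol does not require it. No bias in the primary endpoint is claimed. The sponsor should correct this, because the protocol itself names the hazard and the remedy is cheap. Confidence is medium, since the authors may have regarded acute renal failure and purification as the same group.

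**What to change.** **Preferred.** Amend section 3.4 and the synopsis to exclude acute renal failure at randomisation whether or not blood purification has started, with a threshold chosen by the sponsor. A modified Marshall renal score of 2 or more, the definition of failure in section 5.1, is a ready option, though the documents do not say it was the intended cut-off. Confine the change to renal failure, because the 24-hour rule in 5.1 suggests that other baseline organ failure was meant to remain eligible.

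**Alternative.** If only patients on purification were meant, correct section 10, say whether indicated or planned purification counts, and state how the bleeding risk is handled for the remaining patients. One way is to apply the low-bleeding-risk condition of 4.3 and 4.5 to the three-day course.

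**Cost.** A short wording change, plus the ethics re-review and re-approval that section 6.2 requires, at up to 10 centres. The preferred option costs about 5.5 replacement patients, or 0.36 months, for each 1% excluded. It could also shift the control event rate. On a normal approximation with the relative risk unchanged, power stays at 80% or more down to a control rate of about 14.6%, so a modest fall is affordable. The constant relative risk is an assumption, since the population would change slightly.

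### The oxygenation ratio in the severe-ARDS exclusion is printed as FiO2/PO2 < 60, which is always true at the stated ventilator settings, so the threshold separates no patients

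*Protocol*

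**What the plan says.** Protocol section 3.4 has one exclusion for the most gravely ill: "Patients with irreversible organ failure or other critical manifestations who are expected to die within 24 hours". Three examples follow, one each for lung, circulation and consciousness. The lung example is "severe ARDS requiring extracorporeal life support", and its bracket reads FiO2/PO2 < 60 if PEEP > 10 cm H2O and FiO2 = 100%. FiO2 is the numerator, and no unit is given for PO2.

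The other two examples carry numeric limits that can be applied as printed: a systolic pressure in mmHg with a pH limit at a named vasopressor dose, and a Glasgow score. The synopsis repeats the exclusion without any of the examples, so the ratio appears only once and no second version is available to check it against.

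**The concern.** A threshold in an eligibility criterion should divide patients into those who meet it and those who do not. This one cannot. FiO2 is fixed by the criterion itself, so the ratio depends on PO2 alone, and with PO2 in the denominator the ratio falls as oxygenation improves. A limit of the form 'below 60' is then met by well-oxygenated and poorly oxygenated patients alike.

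What is at stake is a uniform reading of one criterion. The trial is open-label and may use up to 10 centers. One site could apply the bracket as printed, and another could silently turn the ratio round. The bracket is the only measured oxygenation limit in the lung example. Without it, what is left beyond the ventilator settings is judgement.

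**Working it through.** No figure in the protocol needs reproducing; the check is whether the printed inequality can ever be false.

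**Inputs (Protocol section 3.4):** ratio FiO2/PO2; limit 60; FiO2 = 100%, that is 1.0 as a fraction or 100 as a percentage; PEEP > 10 cm H2O, which does not enter the ratio.

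**Assumptions:** PO2 is taken from 20 to 600 mmHg, a range wide enough to cover any survivable value. Because the unit is missing, both mmHg and kPa are tried (1 mmHg = 0.133322 kPa).

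**Step 1. The ratio as printed.**

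| FiO2 as | PO2 in | at PO2 20 mmHg | at PO2 60 mmHg | at PO2 600 mmHg |
|---|---|---|---|---|
| fraction | mmHg | 1/20 = 0.05 | 0.0167 | 0.0017 |
| percent | mmHg | 100/20 = 5.0 | 1.667 | 0.167 |
| fraction | kPa | 1/2.666 = 0.375 | 0.125 | 0.013 |
| percent | kPa | 100/2.666 = 37.5 | 12.5 | 1.25 |

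The largest value is 37.5. Every entry is below 60.

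**Step 2. The PO2 at which the printed inequality would stop being true.** FiO2/PO2 < 60 fails only if PO2 ≤ FiO2/60:

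- fraction, mmHg: 1/60 = 0.017 mmHg
- percent, mmHg: 100/60 = 1.67 mmHg
- fraction, kPa: (1/60)/0.133322 = 0.125 mmHg
- percent, kPa: (100/60)/0.133322 = 12.5 mmHg

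All four lie below the 20 mmHg lower end of the range. The inequality is true for every patient on the stated settings.

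**Step 3. The ratio turned round.** With PO2/FiO2 < 60, FiO2 = 1.0 and PO2 in mmHg, the limit is PO2 < 60 mmHg. Values of 20 and 40 meet it; 60, 80, 100 and so on up to 600 do not. The same number now divides patients, which points to a transposition.

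**Step 4. Why the units must also be stated.** If the reversed ratio were read in kPa, with FiO2 as a fraction, the limit would be 60/0.133322 = 450 mmHg. With FiO2 as 100 and PO2 in mmHg, it would be 60 × 100 = 6000 mmHg, and the threshold would again exclude nothing from its reach. Correcting the orientation alone does not settle the criterion.

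**The case against.** The strongest reply is that the bracket is not a stand-alone rule. It explains an example, severe ARDS needing extracorporeal support, and that example sits under the heading condition of anticipated death within a day. Both conditions still apply when the ratio is inert. This stands. A reader might infer that the criterion collapses to PEEP above 10 on pure oxygen, so that patients with respiratory failure are excluded as moribund. The text does not support that. A patient on those settings with a PO2 of, say, 200 mmHg meets the bracketed inequality, but is excluded only if also considered to need extracorporeal support and to be near death.

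A reader might also link the error to the primary endpoint, because respiratory failure is one of its components. Section 5.1 counts organ failure "defined as a score of 2 or more using the modified Marshall scoring system" and deals with earlier failure by "excluding events occurring within 24 hours before randomization". That is an outcome definition. Organ failure as such is not an exclusion, and section 5.1 contains no second error. Eligibility is also settled before allocation, so a misread criterion would not by itself bias the comparison between arms.

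Finally, few patients are exposed: those within 48 hours of onset and already on these settings. Some of them may also fall under the separate exclusion for impaired capacity to decide. That is an inference, and the protocol elsewhere allows consent by a legal representative, but the direction is fair. Divergence between sites is a possibility and is not documented.

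None of this makes the printed threshold work. The surrounding words limit the damage from a limit that is always met; they do not supply the oxygenation limit that the sponsor evidently meant to set.

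**Conclusion.** The point holds as an error in a stated eligibility threshold. At FiO2 of 100% the printed ratio is at most 37.5 for a PO2 of 20 mmHg or more under every unit convention tried, so the limit of 60 never discriminates. In the lung example, eligibility rests on the ventilator settings and on the investigator's judgement of the need for extracorporeal support and of imminent death. Transposition is the likely explanation, inferred from step 3; no other part of the protocol confirms it.

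The practical size is small. The number of patients on these settings is not given and is assumed to be a small part of the planned 540. No effect on power or on the primary result is claimed, and the protocol does not show that anyone was, or would be, wrongly excluded.

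**What to change.** The sponsor should reconcile the printed ratio with its own limit of 60: confirm which term belongs on top, state the unit of PO2 and whether FiO2 is entered as a fraction or a percentage, and print the result in section 3.4 and in any eligibility item on the case report form, so that all sites apply the same criterion. The clinical limit itself is for the sponsor to confirm, and none is proposed here. If recruitment has begun, it is sensible to look at any screening entries excluded on this item; that is a precaution and does not presume that errors occurred.

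The cost is a one-line correction to the protocol and case report form, with the ethics re-approval that section 6.2 requires for amendments. It needs no extra patients, procedures or analyses.

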## **4 STUDY PROCEDURES**

### **4.1 Randomization and masking**

Patients will be randomly assigned (1:1) to either LMWH plus insulin (LMWH + insulin group) or insulin alone (insulin group). Dynamic randomization will be used via a network-based center random software (Churun Information Technology Co, Ltd, Guangzhou, China). The randomization and masked allocation assignments will be conducted by the sub-investigator from each entity.

